## Abstract

**Background:**

Frailty can be defined as a medical syndrome with multiple causes and contributors, characterized by diminished strength and endurance and reduced physiological function that increases the vulnerability to develop functional dependency and/or death. Studies have shown that the most commonly studied exercise protocol for frail older adults is the multimodal training. Interactive video games (IVGs) involve tasks in virtual environments that combine physical and cognitive demands in an attractive and challenging way. The aim of this study will be to evaluate the feasibility, safety, acceptability, and functional outcomes of playing Nintendo Wii Fit Plus^TM^ (NWFP) for frail older adults.

**Methods/design:**

The study is a randomized controlled, parallel group, feasibility trial. Participants will be randomly assigned to the experimental group (EG) and control group (CG). The EG will participate in 14 training sessions, each lasting 50 min, twice a week. In each training session, the participants will play five games, with three attempts at each game. The first attempt will be performed with the assistance of a physical therapist to correct the movements and posture of the patients and subsequent attempts will be performed independently. Scores achieved in the games will be recorded. The participants will be evaluated by a blinded physical therapist at three moments: before and after intervention and 30 days after the end of the intervention (follow-up). We will assess the feasibility, acceptability, safety, and clinical outcomes (postural control, gait, cognition, quality of life, mood, and fear of falling).

**Discussion:**

Due to the deficiencies in multiple systems, studies have shown that multimodal interventions including motor-cognitive stimulation can improve the mobility of frail elderly adults. IVGs, among them the NWFP, are considered as a multimodal motor-cognitive intervention that can potentially improve motor and cognitive functions in the frail elderly. However, there is still no evidence in the literature that proves the feasibility, safety, acceptability, and functional outcomes of this intervention in frail elderly individuals.

**Trial registration:**

Brazilian Registry of Clinical Trials (RBR-823rst). World Health Organization Trial Registration Data Set (Additional file 1).

**Electronic supplementary material:**

The online version of this article (10.1186/s40814-017-0184-1) contains supplementary material, which is available to authorized users.

## Background

Frailty can be defined as a medical syndrome with multiple causes and contributors, characterized by diminished strength and endurance and reduced physiological function that increases an individual’s vulnerability to develop increased dependency and/or death [1]. A recent systematic review [2], incorporating 31 studies of frailty in persons aged 65 years or older, found a prevalence of from 4.0 to 17.0% (mean 9.9%) of physical frailty, with a higher prevalence when psychosocial frailty was also included. Women (9.6%) were almost twice as likely as men (5.2%) to be frail [1]. The prevalence of frailty is markedly increased in persons older than 80 [1].

Frail older adults have a high risk of becoming dependent; however, with adequate intervention (mainly nutrition and physical exercise), frailty can be reversed to a robust state [3]. A systematic review [4] showed that the best strategy to reduce the number of falls, improve gait and balance, and increase muscle strength in frail elderly individuals is interventions based on combined exercises, such as resistance training, muscle strengthening, flexibility, balance and coordination training, and aerobic exercises.

New types of intervention have been proposed as complementary tools for rehabilitation of the elderly, among them interactive video games (IVGs) that can optimize motor learning and neural plasticity [5]. IVGs combine motor and cognitive tasks which are performed in a motivating and challenging virtual environment [6]. IVGs stimulate complex and dynamic movements that are similar to the movements required in daily life [5]. In addition, IVGs are inexpensive, fun, and can be used by patients who live in remote settings. Together, these factors can help to improve adhesion to and results of rehabilitation [6].

Among IVGs, Nintendo Wii Fit Plus® (NWFP) games have been considered as an inexpensive motor-cognitive intervention. The games are played using the Balance Board, a wireless platform that detects body oscillation through four sensors that identify the center of pressure of the player. A recent systematic review [7] investigated the effects of IVGs on balance of different populations, among them, elderly people. Twelve of the selected studies assessed the effects of the NWFP and showed that the NWFP was effective for improving balance [8–10].

We performed an extensive search in the PubMed, Web of Science, and PEDro databases and found only one pilot study [11] which compared the effectiveness of the NWFP to improve mobility of pre-frail elderly people. The participants were randomized to one of three groups: (1) control, (2) seated exercise (traditional senior fitness program), or (3) NWFP group (basic games and addition of weight vest with 2% of their body weight every 2 weeks). The training of groups 2 and 3 was performed for 45 min, three times a week, for 15 weeks. There was improvement in physical functional status in the seated exercise and NWFP group compared to the control group. Despite the positive effects of the NWFP group, there were some methodological issues in this pilot study such as the absence of blindness of the subjects, therapists, and evaluators and the absence of the intention-to-treat analysis, since there was a dropout of 12 participants during the study. Furthermore, this pilot study did not assess the feasibility, safety, or acceptability of the NWFP for pre-frail elderly people. Finally, the participants of the NWFP group performed their training using a weight vest. The addition of weight certainly interfered in the intensity of the intervention with the games. In fact, the weight addition makes it difficult to infer whether the improvement occurred due to training with the games or the resistance of the weight vest.

Despite evidence of the positive effects of IVGs on clinical outcomes of community dwelling elderly people [12–20], it is not clear whether IVGs are feasible, safe, and acceptable for frail elderly people. Furthermore, the effectiveness of IVGs on this population has not been established.

### Objectives

The current study aims to evaluate the feasibility, safety, acceptability, and functional outcomes of playing NWFP in frail older adults.

### Hypotheses

We speculate that the frail elderly adults will improve their performance in the games and increase their scores;We hypothesize that the intervention based on the NWFP games will not cause any adverse events such as syncope, dizziness, vertigo, falls, or any other medical condition that requires hospitalization or leads to disability. A previous study [24] showed that elderly individuals with Parkinson’s disease presented good acceptability to training with the NWFP;We expect that the NWFP games will be acceptable to frail elderly adults. Despite this population possibly not being familiar with this kind of technology, the NWFP games were developed for entertainment with attractive and motivating virtual environment and are easy to use. A previous study [12] showed that elderly adults demonstrated good acceptability to training with NWFP;The training sessions with the NWFP will provide improvement in postural control, gait, quality of life, cognition, and mood.

### Trial design

The study will be a randomized controlled, parallel group, feasibility trial. Participants will be randomly assigned 1:1 to NWFP training or usual care. Study assessments will be conducted before and after the intervention and 30 days after the end of the intervention (follow-up).

## Methods

### Study setting

All participants will be recruited from the Frailty Ambulatory Clinics at the Hospital of the Medical School, University of Sao Paulo, Brazil.

### Eligibility criteria

#### Inclusion criteria

Pre-frail and frail older adults aged 60 years or older, diagnosed with frailty syndrome according to Fried’s criteria: slow walking speed, impaired grip strength, self-reports of declining activity levels, exhaustion, and unintended weight loss (pre-frail—presence of at least one deficit and frail—presence of at least three deficits) [21];Capacity to maintain a standing position and walk independently;Normal or corrected visual acuity evaluated by the Snellen Scale [22];Good hearing acuity, clinically assessed by the whisper test [23] without previous experience with the NWFP;Agreement to participate by signing the informed consent form.

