### Outcome measures

#### Feasibility, acceptability, and safety outcomes

Feasibility will be assessed by the participants’ performance in the games, measured by the score achieved. Increasing scores indicate that the participant is capable of not only playing but also improving his or her performance in the games. This is the main measure of game play that promotes motivation [24]. To determine the feasibility of the program, we will collect attendance records from each participant before and after training sessions. We will consider the exercise program to be feasible if we maintain > 50% attendance for all sessions and average > 80% attendance per session.

Acceptability will be assessed through a game satisfaction questionnaire [25]. The questionnaire consists of 18 questions, among them are participants’ perception of games (“What do you like about the games?”; “Which game do you like best?”; “Which game do you like least?”); more difficult games (“Which game did you find most difficult?”); easier games (“Which game did you find easiest?”); motivation (“Did you feel motivated to play the games?”); and discomfort during training (“Did you feel any discomfort playing the games?”).

Safety will be assessed by the proportion of participants who experienced intervention-related adverse events or any serious adverse event during the study period. An adverse event is defined as any untoward medical occurrence, such as convulsions, syncope, dizziness, vertigo, falls, or any other medical condition that requires hospitalization or leads to disability. The therapist will register the occurrence of any adverse events, and the participant’s blood pressure, oxygen pulse saturation, heart and respiratory rates, and self-perception of effort, measured by the BORG Scale [26], will be assessed before and after each training session. We will monitor the onset of any clinical conditions that could preclude the performance of physical exercises in an orthostatic position, such as cardiovascular, orthopedic, or neurological conditions.

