### Randomization

Participants will be randomly assigned to the EG and CG, with an allocation ratio of 1:1. Randomization schedule will be prepared from a computer-generated list of random numbers, by a researcher not involved in the trial. In order to guarantee the balance between the groups regarding the level of frailty, we will stratify pre-frail and frail participants in the randomization.

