## Discussion

The current study is designed to evaluate the feasibility, safety, acceptability, and functional outcomes of playing NWFP for frail older adults. This feasibility study is in preparation for a main trial that will go ahead if all feasibility criteria and hypothesis are met.

Frailty affects functionality in different aspects, such as mobility, gait, balance, muscle strength, motor processing, cognition, nutrition, and physical activity [38]. Due to the deficiencies in multiple systems, studies have shown that multimodal interventions including motor-cognitive stimulation can improve the mobility of frail elderly adults [39]. IVGs, among them the NWFP, are considered as a multimodal motor-cognitive intervention that can potentially improve motor and cognitive functions in the frail elderly. The NWFP can promote physical activity and improve balance, mobility, gait speed, muscle strength, flexibility, and functional abilities in older adults [40]. However, there is still no evidence in the literature that proves the feasibility, safety, acceptability, and functional outcomes of this intervention in frail elderly adults. We speculate that due to the challenging stimulation to the postural control and cognitive systems, added to factors that can improve motor learning such as visual and auditory feedback and motivating environment, the NWFP will be feasible, safe, and acceptable and will promote clinical benefit in frail elderly adults.

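### The stated question and conclusions are about frail adults, but pre-frail adults are enrolled too and feasibility is judged without regard to frailty level

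*Protocol article*

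**What the plan says.** The Objectives section asks about feasibility, safety, acceptability and "functional outcomes of playing NWFP in frail older adults". Under Hypotheses, the statements on game performance and on acceptability also name frail elderly adults. The Discussion expects that "the NWFP will be feasible, safe, and acceptable and will promote clinical benefit in frail elderly adults", and makes a main trial conditional on all feasibility criteria and hypotheses being met.

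The Inclusion criteria admit "Pre-frail and frail older adults aged 60 years or older" and define the two levels as "pre-frail—presence of at least one deficit and frail—presence of at least three deficits". The Randomization section says "we will stratify pre-frail and frail participants in the randomization", and gives the purpose as "In order to guarantee the balance between the groups regarding the level of frailty". No section sets an expected mix, a minimum number of frail participants or a cap on pre-frail ones.

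Under Feasibility, acceptability, and safety outcomes, the programme counts as feasible if the trial can "maintain > 50% attendance for all sessions and average > 80% attendance per session". Safety is the proportion of participants with an intervention-related or serious adverse event. Neither is tied to frailty level.

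**The concern.** The population in the question is narrower than the population enrolled. Randomization treats pre-frail and frail as different enough to stratify on, yet the criteria that decide feasibility, and with it the main trial, are worded for everyone together. If attendance or game performance differs by frailty level, a pass in the whole group can be credited to frail adults who did not themselves reach the threshold. At stake is whether a main trial in frail adults rests on evidence from frail adults.

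A second, smaller problem lies in the definitions. Pre-frail has no upper bound, so on a literal reading a person with three or more deficits belongs to both levels. This variable decides which randomisation stratum a participant enters.

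**Working it through.** **Sample size.** The Sample size section gives 12 participants per group with full data and 20% dropout. 12 / (1 − 0.20) = 15 per group, 30 in total, which reproduces the plan's figure. The experimental group therefore has n = 15. The plan does not give the frail share, so every split below is an assumption.

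**Attendance.** Pooled attendance is (n_pre × a_pre + n_frail × a_frail) / 15.
- Assumed: 10 pre-frail at 90%, 5 frail at 65%.
- (10 × 0.90 + 5 × 0.65) / 15 = (9.00 + 3.25) / 15 = 12.25 / 15 = 81.7%.
- The pooled average passes 80%; the frail participants are 15 percentage points below it. Because 65% exceeds 50%, the example is not caught by the 50% condition even if that is applied to participants at these averages.

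Frail attendance at which the pooled average equals 80%, with pre-frail attendance assumed to be 90%, is (0.80 × 15 − 0.90 × n_pre) / n_frail:

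| Frail | Pre-frail | Frail attendance at break-even |
|---|---|---|
| 10 | 5 | (12 − 4.5) / 10 = 75.0% |
| 8 | 7 | (12 − 6.3) / 8 = 71.3% |
| 5 | 10 | (12 − 9.0) / 5 = 60.0% |
| 4 | 11 | (12 − 9.9) / 4 = 52.5% |

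The gap is small when most participants are frail and grows as their share falls.

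**Safety.** With zero events in n participants, the upper limit of the exact two-sided 95% interval is 1 − 0.025^(1/n).
- n = 15: 21.8%
- n = 8: 36.9%
- n = 7: 41.0%
- n = 5: 52.2%

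Zero events overall means zero events among frail participants, so nothing is concealed. Only the precision changes.

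**Stratum definitions.** Applying both definitions to each possible count of the five Fried criteria:

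| Deficits | Meets pre-frail | Meets frail |
|---|---|---|
| 0 | no | no |
| 1 or 2 | yes | no |
| 3, 4 or 5 | yes | yes |

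The levels overlap at three or more, and no rule of precedence is stated.

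**The case against.** The strongest reply is that frail is used loosely. The Inclusion criteria describe both levels as having frailty syndrome, so the label may simply mean everyone enrolled, and readers can see who was eligible. That explains how the mismatch arose. It does not remove it, because the same document separates the two levels for randomisation, and a reader of the conclusion would take frail in that narrower sense.

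A reader might infer that the data will be mainly pre-frail. The documents do not support this: no mix is given, and all recruitment is from a hospital's frailty clinics. The 10:5 split and the attendance rates above are illustrations only, and no passage says that pre-frail people attend better.

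A reader might also infer that enrolling pre-frail people contradicts the Background, because the one earlier pilot of these games was in pre-frail people. The Background does not give that as the reason for the gap. It notes that the pilot left feasibility, safety and acceptability in pre-frail people unassessed, so including them is legitimate.

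Nor can pooling mask a safety failure. The hypothesis is that the intervention causes no adverse events, and any such event in a frail participant contradicts it whatever the mix. No safety threshold is set that the wider limits would breach.

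On the definitions, stratifying on two distinct levels makes sense only if three or more deficits means frail, and the number of Fried criteria is recorded at baseline, so assignments can be checked. The overlap is most likely a slip of wording.

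Finally, by-stratum tables are usually left to the analysis plan, which is promised and not shown. Their absence is not the fault. The fault is in what the article itself fixes: the stated population, the definitions, and decision criteria that ignore frailty level.

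**Conclusion.** The point holds as a mismatch between the population in the question and conclusions and the population enrolled, with feasibility criteria that do not distinguish frailty level. Its effect depends on an unknown mix. Under the assumed 10:5 split, a pooled 81.7% would pass while frail attendance was 65%; with 10 of 15 frail and pre-frail attendance at 90%, frail attendance would have to be at least about 75% for a pooled pass, so the possible error is modest. For safety the loss is one of precision only, from an upper limit of 22% with 15 participants to 52% with 5. The overlap in definitions is literal and probably unintended, but should be corrected because it governs the strata.

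**What to change.** State the objective, hypotheses and conclusions for pre-frail and frail older adults. Write the strata as mutually exclusive: one or two deficits versus three or more. Check the strata already assigned against the recorded number of Fried criteria, since about half the participants had been recruited.

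Describe attendance, game scores and adverse events by randomisation stratum with 95% confidence intervals, exact binomial for proportions of participants. Attendance and scores repeat within a person, so their intervals should be based on participant-level summaries. Limit any claim specific to frail adults to the frail stratum. No hypothesis test and no extra participants are needed.

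The cost is a formal amendment, because the Protocol amendments section requires agreement of the ethics committee and the trial registry for changes to objectives, and frail-only estimates that will be visibly imprecise. The data needed are already collected.

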### Exclusion criteria

Participants presenting with clinical conditions that could preclude the performance of physical exercises in an orthostatic position, such as cardiovascular, orthopedic, or neurological conditions, and older adults unable to interact with the games.

### Administration of assessments

The same-trained researcher will provide the patient with a free informed consent form, which also contains information on the possible benefits that the interventions may bring and possible risks and indemnities to patients, also emphasizing that the patient can withdraw from the research at any time without any contradictions. On the same day, the evaluator will clarify all doubts regarding the research project and inform the volunteers that all data resulting from the survey will be used for scientific purposes. The same-trained researcher, blinded to treatment allocation, will evaluate all participants at three timepoints: immediately pre and post interventions and 30 days after the end of the interventions (follow-up). Participants will be asked not to inform the evaluators about the kind of intervention they have received.

### Intervention

Participants will be randomly assigned to the experimental group (EG) and control group (CG), with an allocation ratio of 1:1.

Participants in the EG will participate in 14 training sessions, lasting 50 min, with a frequency of twice a week. In each training session, the participants will play five games and will be allowed three attempts at each game. The first attempt will be performed with the help of a physical therapist to correct the movements and posture of the patients through manual steering and verbal controls, while the subsequent attempts will be performed independently for the analyses of motor learning. Scores achieved in the games will be recorded. The time required to exchange the game will be approximately 2 min, and the patients will sit in a chair during this period.

Participants in the CG will be guided through verbal instructions and an illustrative booklet of guidelines carried out according to the World Health Organization, Policy Department number 385, 2014. This booklet describes physical activity, its benefits and risks, and encourages the study participants to seek health units near their residence where free physical activities are offered.

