### Participant timeline

Table 2 illustrates the process of enrolling participants in the study, the intervention, and timing of assessments.

**Table 2 Tab2:** Schedule of enrolment, interventions, and assessments

	Study period				
Timepoint	Day 1	Day 2	Days 3 to 16	Day 17	Day 47
Enrollment	X				
Eligibility screen	X				
Informed consent	X				
Allocation	X				
Interventions			X		
Assessments		X		X	X
Initial assessment (pre)		X			
Final assessment (post)				X	
Follow-up assessment					X

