### Blinding

Blinding of trial participants and the intervention facilitator is not possible. All outcomes will be assessed by a researcher blinded to group allocation. Participants will be asked not to disclose their allocation to the physical therapist who will participate in the assessments.

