### Statistical analyses

A detailed analysis plan will be prepared before all the data has been collected. Analyses will be conducted in Dell™ Statistica (version 13.0) using the principles of intention-to-treat. Descriptive statistics will be used to characterize the groups at baseline and present the feasibility outcomes. Although determining differences in clinical outcomes between the two groups is not the primary purpose of this trial, comparisons will be undertaken to investigate the feasibility of studying these outcomes and calculate estimates for the likely effect sizes and 95% confidence intervals. The effect size will be calculated in order to determine whether change can be detected over time using these outcome measures and to determine the most appropriate primary outcome. The focus of the results will be on the estimates of the treatment effects rather than statistical significance, and as such, no hypothesis testing will be undertaken [37]. Differences between the two comparison groups will be presented in the form of an unadjusted mean difference for continuous outcomes with their associated 95% confidence intervals.

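### Table 2's day numbers contradict the stated training schedule: 14 sessions at two per week put the post assessment at about Day 47 to 52 and the follow-up at about Day 76 to 82, not Day 17 and Day 47

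*Protocol article*

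**What the plan says.** The training schedule is given twice in the protocol article. The abstract (Methods/design) says "The EG will participate in 14 training sessions, each lasting 50 min, twice a week", and the Intervention section repeats it: "Participants in the EG will participate in 14 training sessions, lasting 50 min, with a frequency of twice a week".

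The timing rule for assessments is also given twice. Trial design says "Study assessments will be conducted before and after the intervention and 30 days after the end of the intervention (follow-up"), and Administration of assessments says "immediately pre and post interventions and 30 days after the end of the interventions (follow-up").

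Participant timeline then introduces a day-by-day schedule: "Table 2 illustrates the process of enrolling participants in the study, the intervention, and timing of assessments". Table 2 has one set of columns for both arms:

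- Day 1: enrolment, eligibility, consent and allocation
- Day 2: initial assessment
- Days 3 to 16: interventions
- Day 17: final assessment
- Day 47: follow-up

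The article does not say that a day in this table means anything other than a calendar day.

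The control arm has no training sessions: "Participants in the CG will be guided through verbal instructions and an illustrative booklet of guidelines".

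**The concern.** The table offered as the timing of the trial cannot be reconciled with the training schedule in the text. Fourteen sessions at two per week take seven weeks, while the table allows two weeks.

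The two arms are affected differently. For the experimental group a reader can set the table aside and count from the last session. A control participant has no last session, and the article gives no other date for the end of the intervention. Table 2 is therefore the only numeric schedule for that arm, and its numbers are wrong.

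What is at stake is comparability in time. Statistical analyses says: "Differences between the two comparison groups will be presented in the form of an unadjusted mean difference". The same section uses effect sizes to help choose a primary outcome for later work. Those estimates are readable only if both arms are measured at the same elapsed time from baseline.

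**Working it through.** **Inputs.** 14 sessions at 2 per week (Abstract; Intervention). First session on Day 3, post assessment on Day 17, follow-up on Day 47 (Table 2). Follow-up 30 days after the intervention ends (Trial design; Administration of assessments).

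**Reproducing the table.** Days 3 to 16 inclusive are 16 − 3 + 1 = 14 days, the same number as the sessions. The post assessment is the next day, 16 + 1 = 17. The follow-up is 17 + 30 = 47. So the table's figures come out if each session takes one day and 30 calendar days are then added.

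**Can these be calendar days?** Days 3 to 16 are 14 / 7 = 2 weeks. At two sessions per week they hold 2 × 2 = 4 sessions, or 4/14 = 29%, whatever the spacing within the week. Fitting all 14 would need one session per day, that is 7 per week.

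**Can they be visit numbers?** Enrolment (1) + initial assessment (1) + sessions (14) + post assessment (1) = 17, which matches Day 17. The follow-up would then be contact 18, not 47. No single unit fits every column.

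**Dates under the stated schedule.** Training takes 14 / 2 = 7 weeks. Let g be the gap in days between the two sessions of a week. The first session of week 7 is on Day 3 + 6 × 7 = 45, so session 14 is on Day 45 + g. The post assessment is taken as the next day, Day 46 + g. The follow-up is Day 75 + g if counted from session 14, or Day 76 + g if counted from the post assessment.

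| g | Session 14 | Post | Follow-up | Sessions by Day 16 |
|---|---|---|---|---|
| 1 | Day 46 | Day 47 | Day 76 or 77 | 4 |
| 2 | Day 47 | Day 48 | Day 77 or 78 | 4 |
| 3 | Day 48 | Day 49 | Day 78 or 79 | 4 |
| 4 | Day 49 | Day 50 | Day 79 or 80 | 4 |
| 5 | Day 50 | Day 51 | Day 80 or 81 | 4 |
| 6 | Day 51 | Day 52 | Day 81 or 82 | 4 |

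**Difference from Table 2.**

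- Post assessment: 47 − 17 = 30 to 52 − 17 = 35 days.
- Follow-up: 76 − 47 = 29 to 82 − 47 = 35 days.

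Calendar Day 47, the table's follow-up, therefore lies at about the end of training rather than 30 days after it.

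**The case against.** The strongest reply is that this is a labelling slip with the right rule stated elsewhere. The text gives the session count, the frequency and the assessment rule twice each, and the likely origin of the table's numbers is easy to see. For the experimental group this stands: a reader can tell which source governs and recover the correct timing.

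A second reply is that a condensed article may leave the control arm's visit dates to the full protocol. That also stands, and the lack of a separate control schedule would not be a finding by itself. The point is narrower: the article does print a schedule covering both arms, and that schedule is wrong.

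A third reply concerns consequences. A reader might infer that controls are seen about a month earlier than the trained arm and that the between-group estimates are biased. The article does not support this. Table 2 has one set of columns, and Blinding says "All outcomes will be assessed by a researcher blinded to group allocation", so equal timing appears to be intended. If timing is equal in practice, the wrong labels bias nothing. Statistical analyses also says that clinical differences are not the main purpose and that no hypotheses will be tested.

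Finally, a reader might fix the dates more tightly, at Day 49 to 50 and Day 78 to 80. Those hold only for gaps of 3 and 4 days. A Monday and Wednesday pattern, for example, gives Day 48 and Day 77 or 78.

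**Conclusion.** The inconsistency is real, and no single reading of the day labels removes it. Under the stated frequency, Day 17 is 30 to 35 days too early for the post assessment and Day 47 is 29 to 35 days too early for the follow-up.

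These figures assume a first session on Day 3, two sessions in every week, and a post visit the day after session 14. A later start, or missed sessions made up at the end, would move the dates later still. The finding that only 4 of 14 sessions fit in Days 3 to 16 needs only the first of these assumptions and the stated frequency.

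The impact is modest. Unequal timing between the arms is a risk that the table leaves open, not a practice that the article shows. Sample size, attendance, game scores and acceptability are unaffected. The table should still be corrected, because it is the only numeric schedule for the control arm and this work is meant to inform a definitive trial.

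**What to change.** Restate Table 2 in calendar time: training in weeks 1 to 7, post assessment at the end of week 7, follow-up 30 days later. Add one sentence saying that the same times from baseline apply to both arms, so that for a control participant the intervention ends at the end of week 7.

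Before adding that sentence, check the assessment dates of participants already enrolled. Trial status puts recruitment at about 50%, or roughly 0.5 × 30 = 15 people. If the arms were seen at the same times, the sentence simply records what was done. If not, say so, report the actual interval from baseline by arm, and use the shared times for the remaining participants.

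The cost is one relabelled table, one sentence and a check of existing visit dates, with no extra visits, staff or participants. If the full protocol carries the same table, correcting it there may need the formal route described in Protocol amendments.
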